**BIOMARKER COLLECTION**						
Blood sample	C	10	X	X	X	X
Saliva sample	C	5–10		X	X	X
CSF sample	C	N/A	X			
Injury information	EMR	N/A	X			
Demographics	P	15		X	X	X
**CHILD FUNCTION**						
BRIEF-2	P	10		X^†^	X	X
SDQ	P	10–15		X^†^	X	X
Vineland-3	P	10–15		X^†^	X	X
NIHTB-CB	C	30–45		X	X	X
**CHILDHOOD ADVERSITY**						
PAT	P	5–10		X	X	X
CHIP	P	10–15		X^†^	X	X
**POTENTIAL COVARIATES/CONFOUNDERS**						
Pubertal status self-report	C	5		X	X	X
Tobacco/nicotine self-report	C	5		X	X	X
Caregiver tobacco/nicotine screener	P	5		X	X	X

† *Retrospective ratings by parent at acute assessment to assess premorbid functioning*.

*BRIEF-2, Behavior Rating Inventory of Executive Function, Second Edition; C, child; CHIP, Child Health and Illness Profile; CSF, cerebrospinal fluid; EMR, electronic medical record; NIHTB-CB, NIH Toolbox-Cognition Battery; P, parent; PAT, psychosocial assessment tool*.

Families are compensated for their time at the acute and follow-up visits and reimbursed for parking and transportation costs. Multiple methods are used to track and contact participants and reduce attrition.

### Measures

Table 1 provides an overview of study measures organized by domain, source of data, and assessment occasion.

### Hypothesized Predictors

#### Demographics

Child and family demographic information is collected at both the acute time point and at the 6- and 12-month follow-ups. Parents answer questions about the child and family members' age, sex, race, ethnicity, and relationship to the child (e.g., biological parent, legal guardian, etc.), as well as socioeconomic status (e.g., family income, parent education level, parent employment, use of financial assistance programs), household composition, and marital status.

#### Injury Information

The study staff extract information about the characteristics of the child's injury from their EMR. Specifically, the child's initial, postresuscitation, and best in 24-h GCS scores, MRI or CT findings, date and time of injury, and mechanism of injury are noted.

#### Preinjury Child Function

At the acute visit, parents report on their child's preinjury functioning through retrospective recall. The efficacy of this method has been demonstrated in previous studies (86, 87).

To assess everyday executive functioning, parents complete the Behavior Rating Inventory of Executive Function, Second Edition (BRIEF-2) or Preschool Version (BRIEF-P) (88, 89). Three composite scores are computed for behavioral regulation, emotion regulation, and cognitive regulation, as well as a global executive composite.

The Strengths and Difficulties Questionnaire (SDQ) measures psychological adjustment. Subscales include Emotional Symptoms, Conduct Problems, Hyperactivity–Inattention, Peer Problems, and Prosocial Behavior. A Total Difficulties score is also provided. Four different versions are administered based on the child's age.

Adaptive functioning is measured using the Vineland Adaptive Behavior Scales, Third Edition (Vineland-3). Parents complete items designed to assess their child's ability to perform day-to-day activities in the domains of Communication, Daily Living, and Socialization. Composite scores are computed for each domain, as well as a general Adaptive Behavior Composite (90).

#### Childhood Adversity

Parents complete the Psychosocial Assessment Tool (PAT) as a measure of psychosocial risk and childhood adversity, particularly in the context of the family in a pediatric setting. The PAT evaluates a variety of domains: family structure and resources, social support, patient, sibling, and caregiver problems (internalizing, externalizing, social, cognitive), family beliefs, and caregiver stress reactions. Subscale scores are calculated for each of these domains, as well as a total PAT score (91).

Resilience may buffer the effects of childhood adversity (92) and has recently gained interest in predicting outcomes following TBI (93, 94). Parents complete the Resilience items from the Child Health and Illness Profile (CHIP), child edition (6–11 years; 19 items) or adolescent edition (12–18 years; 38 items) (95, 96). The Resilience domain measures the parent's assessment of the child's family involvement, social problem solving, and physical activity.

### Biomarker Collection and Processing

CSF is collected by the bedside nurse into a CSF vial and refrigerated until processing within 48 h by the CHP PCTRC. Processing involves separation and aliquoting of supernatant for future protein level analysis and the cell pellet for genetic and epigenetic analysis. Processed samples are stored at −80°C.

Acute blood samples are collected by the child's bedside nurse from his or her IV if patent or via venipuncture with parent and child permission. Chronic blood samples are collected via venipuncture by a PCTRC nurse. Up to 10 cc of blood is collected at each draw into ethylenediaminetetraacetic acid (EDTA) vacuum tubes and refrigerated until processing within 48 h by the PCTRC. Processing involves separation and aliquoting of plasma for future protein level analysis and the buffy coat (leukocytes) for DNA extraction using a simple salting protocol for genetic and epigenetic analysis. Processed samples are stored at −80°C.

Up to 2 ml of saliva is collected by the study staff using Oragene DNA sample collection kits (DNA Genotek, Ontario, Canada). To collect saliva, the child spits into the Oragene collection tube for 2–5 min until liquid saliva reaches the fill line. If the child is unconscious or unable to spit, study staff instead use a sponge to gently swab the child's gums and inner cheeks and then wring the saliva out of the sponge into the collection tube until the fill line is reached. The study staff then close the tube's lid to release the stabilizing liquid and store the sample at ambient temperature until processing. DNA is extracted using the reagents and protocol from the manufacturer.

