Aim 1: Examine differences between TBI and OI in *BDNF* methylation and BDNF protein levels over the recovery period. We hypothesize that *BDNF* methylation will be higher, and BDNF protein levels will be lower, in children with TBI relative to OI at all time points, and that *BDNF* methylation will decrease, and BDNF protein levels will increase, in the TBI group over time but will remain relatively stable in the OI group.Aim 2: Characterize trajectory classes of *BDNF* methylation and BDNF protein levels following TBI while controlling for potential demographic, injury, and lifestyle covariates. We hypothesize the presence of at least two *BDNF* methylation trajectory classes and two BDNF protein level trajectory classes representing varying degrees of recovery from TBI. We will explore age, sex, pubertal status, TBI severity, overall injury severity, body mass index (BMI), and smoking as potential covariates.Aim 3: Test the indirect effect of childhood adversity on neurobehavioral recovery following pediatric TBI, as mediated by *BDNF* methylation and BDNF protein level trajectory classes.

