Data are collected at three time points postinjury. Acute data collection occurs before hospital discharge, and chronic data collection occurs at 6 and 12 months postinjury during outpatient follow-up visits to CHP. Data are collected pertaining to hypothesized predictors of neurobehavioral recovery (e.g., demographics, injury information, child premorbid functioning, childhood adversity, and biomarkers), neurobehavioral outcomes (e.g., neuropsychological test performance, parent-rated neuropsychological, emotional/behavioral, and adaptive functioning), and potential covariates/confounders (e.g., BMI, pubertal status, tobacco/nicotine exposure, bodily injury severity). Recruitment began in July 2017 and will occur for ~6 years, with data collection complete by mid-2023.

DNA methylation patterns are tissue specific and reflect the local environment of each cell type, and examination of brain tissue is not feasible in patients who survive their injuries; therefore, determining which types of biosamples serve as effective proxies for the CNS environment is an important methodological consideration. Moreover, to be useful as a clinical biomarker, markers must be found in readily accessible biosamples, such as blood or saliva. Several previous studies have shown that methylation in peripheral biosamples, including blood and saliva, is strongly correlated with methylation in brain tissue or CSF (46, 76–81) for several target genes, including *BDNF* (46, 77). Methylation measured in peripheral biosamples may be of even greater prognostic value in TBI compared to neuropsychiatric conditions because brain-specific biomarkers may enter blood circulation in TBI not only through disruption to the blood–brain barrier but also through the glymphatic system (82). Finally, a recent review of the “tissue issue” concluded that the limitations of examining epigenetic brain biomarkers in peripheral tissues or biosamples are surmountable and discussed methodological advantages of using peripheral biosamples: serial biosampling, longitudinal study designs and related causal modeling options, large participant sample sizes yielding statistical power to detect modest effects, and translational utility in clinical settings (83).

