### Study Procedures

The study staff screen the CHP electronic medical record (EMR) daily to identify children who are potentially eligible for study participation. Children are housed in one of two settings when they are identified: (1) the acute care trauma unit or (2) the pediatric intensive care unit (PICU). Children housed in the acute care trauma unit within the first week of their injury are approached about the study. The study staff approach families and conduct brief interviews about the child's preinjury functioning and medical history to confirm eligibility and obtain informed consent prior to any data collection. Interested parent(s) of minor children, and 18-year-old patients capable of consenting on their own behalf, provide written informed consent. Children over the age of 8 capable of understanding study procedures provide assent.

Children with more severe injuries are sometimes housed in the PICU during the acute biosample window (i.e., 1 week postinjury). If a potentially eligible child is in the PICU, the bedside nurse collects the acute blood sample at the same time as a clinical blood draw, before consent has been obtained per an Institutional Review Board (IRB)-approved waiver of informed consent. In addition, if a child with severe TBI has an EVD placed as part of routine clinical care, the bedside nurse collects daily CSF samples up to 1 week postinjury prior to study consent. Families of children whose samples are collected preconsent are approached about study participation once the child is medically stable, usually after discharge to the acute care trauma unit. If the family declines to participate or the child is discovered through screening questions to be ineligible, the preconsent samples are destroyed. Destruction of preconsent samples is requested by the research coordinator and completed by research nurses in the CHP Pediatric Clinical and Translational Research Center (PCTRC). Documentation of sample destruction is maintained both by the PCTRC and by the research coordinator.

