### Data Analyses

#### Biomarker Analysis

DNA extracted from saliva, blood, and CSF will be processed for methylation analysis. We currently plan to use EpiTect Methyl II PCR assays (Qiagen, Germantown, MD) to assess targeted methylation sites in and around the *BDNF* gene; however, due to rapid changes in technology for this type of data collection, when data collection is to begin, we will evaluate whether this method remains our best choice. We will target a select number of *BDNF* CpG islands for this initial study that showed the strongest correlation between blood and CSF in our preliminary data (109) and show significant correlations between *BDNF* methylation in blood and postmortem prefrontal cortex brain tissue according to the searchable online Blood Brain DNA Methylation Comparison Tool (110). Additional *BDNF* methylation targets may be examined in secondary analyses. The resulting data will estimate the methylation level at each CpG site by beta values (i.e., percent methylation). Beta values range from zero to 1, with zero indicating a null methylated site and 1 indicating a fully methylated site. *M* values will then be calculated and used in statistical analysis. (111, 112) Plasma BDNF protein levels will be measured using an ELISA kit according to the manufacturer's instructions. BDNF ELISA kits are available from several manufacturers (e.g., RayBiotech, R&D Systems). We will select a manufacturer at the time of analysis based on available specifications. For quality control, biosamples will be batch analyzed, assays will include biological duplicates and technical replicates, and data will be evaluated by two individuals blinded to phenotype.

Before our main analyses, we will examine the concordance of *BDNF* methylation across saliva, blood, and CSF and compare the predictive value of epigenetic results across biosample types. Based on these results, we may determine that saliva or blood biosamples are more informative than the other, and these results will guide which biosample(s) are used for measurement of *BDNF* methylation in our primary analyses.

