#### Statistical Methods and Power

##### Aim 1: Examine differences between TBI and OI in BDNF methylation and BDNF protein levels over the recovery period

Unadjusted *BDNF* methylation and protein levels will be compared between TBI and OI groups using mixed effects analysis of variance (ANOVA; time as within effect; group as between effect). Mixed effects ANOVA allows for the modeling of effects on continuous outcomes (BDNF methylation and protein levels), is flexible with missing data, and provides explicit estimation of between group and within group variance. We will use appropriate transformations if normality is violated. We expect a significant group × time interaction and group differences at each time point. Alpha will be set at 0.05, and we will adjust for multiple comparisons using Bonferroni corrections. We expect sufficient power (≥0.8) to detect even a small interaction effect (partial η^2^ = 0.01) assuming correlation of 0.5 between repeated measures (G^*^Power 3.1.9.2).

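### Saliva is spat or sponged according to the child's condition, and no stated methylation model has a term for the collection method

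*Protocol article*

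**What the plan says.** Biomarker Collection and Processing gives two ways to obtain saliva. By default, "the child spits into the Oragene collection tube for 2–5 min until liquid saliva reaches the fill line". The alternative is "If the child is unconscious or unable to spit, study staff instead use a sponge to gently swab the child's gums and inner cheeks", after which the sponge is wrung into the same tube to the same fill line. Saliva is scheduled after consent at the acute visit and again at 6 and 12 months (Table 1).

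The Study Overview states the premise that makes the cell source relevant: "DNA methylation patterns are tissue specific and reflect the local environment of each cell type".

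Which biosample carries the methylation analysis is still open. Biomarker Analysis says that saliva, blood and CSF will be compared and that "these results will guide which biosample(s) are used for measurement of *BDNF* methylation in our primary analyses".

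For Aim 1, Statistical Methods and Power says: "Unadjusted *BDNF* methylation and protein levels will be compared between TBI and OI groups using mixed effects analysis of variance". The hypothesis at the end of the Introduction is that *BDNF* "methylation will decrease, and BDNF protein levels will increase, in the TBI group over time but will remain relatively stable in the OI group". The Aim 2 section lists seven covariates to be tested: age, sex, pubertal status, TBI severity, overall injury severity, BMI and smoking. Collection method is not among them.

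**The concern.** By the plan's own premise, a sample sponged from gums and cheeks and a spat sample cannot simply be assumed interchangeable, yet both enter the analysis as saliva. The choice between them is not random. One of its two triggers, unconsciousness, belongs to TBI, because the OI group must show no sign of brain injury. That trigger should also be largely acute. Some TBI children may therefore be sponged at the acute visit and spit at 6 and 12 months.

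If sponging raises measured methylation, the result is a TBI mean that starts high and falls while OI stays level, which is the Aim 1 hypothesis. If sponging lowers it, a real effect of that shape is hidden. An unadjusted model cannot separate the two. TBI severity, tested in Aim 2, is fixed per child and cannot absorb a switch between visits.

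Saliva is a realistic choice for the primary analysis. Children who refuse blood collection are retained, and families who decline a follow-up visit may return a saliva sample by mail.

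**Working it through.** **Inputs from the document.** Follow-up sample of 150 TBI and 75 OI; three visits; alpha 0.05; correlation 0.5 between repeated measures; planned interaction effect partial η² = 0.01; stated power at least 0.8.

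**Assumed inputs, not in the document.** p is the share of TBI children sponged acutely, with none sponged in OI or at follow-up. d is the sponge-minus-spit difference in SD units.

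**Step 1: reproduce the stated power.** f² = 0.01/0.99 = 0.0101. With the G*Power default for a within-between interaction, λ = f² × N × m/(1 − ρ) = 0.0101 × 225 × 3/0.5 = 13.64, with 2 and (225 − 2) × 2 = 446 degrees of freedom. Power is 0.919, so the stated figure reproduces. If 0.01 is instead taken as a partial η² that already includes the correlation, λ = 0.0101 × 223 × 2 = 4.50 and power is 0.458. The stated power therefore points to the default reading.

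**Step 2: put the artefact into the same test.** With no true group or time effect, sponging moves only the acute TBI mean, by s = p × d. Then λ = [150 × 75/225] × (2/3)s²/(1 − 0.5) = 50 × (2/3)s²/0.5 = 66.7s². For p = 20% and d = 1, s = 0.20 and λ = 2.67.

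Chance of a false group-by-time finding at nominal 0.05, before any Bonferroni correction:

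| Sponged share of TBI | d = 0.5 SD | d = 1 SD | d = 2 SD |
|---|---|---|---|
| 5% | 0.05 | 0.06 | 0.10 |
| 10% | 0.06 | 0.10 | 0.29 |
| 20% | 0.10 | 0.29 | 0.84 |
| 30% | 0.18 | 0.58 | 0.995 |

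The 30% row and the 2 SD column show the range and are not expected values. Since only s² enters, the sign of d does not change the rejection rate. It decides whether the artefact resembles the hypothesis or opposes it.

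**Step 3: compare with the planned effect.** The acute TBI shift that equals the planned effect is s = √(13.64/66.7) = 0.45 SD under the default reading, or √(4.50/66.7) = 0.26 SD under the other. At p = 20%, a d of 0.5 to 1 SD gives s = 0.10 to 0.20 SD, which is smaller than either.

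**Step 4: check the remedy.** A simulation of 1,500 runs per setting at p = 20%, with sponging drawn child by child, gave these rejection rates:

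| d | No method term | With method term |
|---|---|---|
| 0.5 SD | 0.118 | 0.050 |
| 1 SD | 0.286 | 0.051 |
| 1.5 SD | 0.514 | 0.054 |

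The Monte Carlo standard error near 0.05 is √(0.05 × 0.95/1,500) = 0.006, so the adjusted rates are consistent with nominal.

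**The case against.** The strongest case against is that the exposure may be small. Acute saliva is taken only after consent, and families of PICU children with preconsent samples are "approached about study participation once the child is medically stable, usually after discharge to the acute care trauma unit". The same postconsent visit schedules a child-completed cognitive battery on an iPad. Sponging may thus be a rare fallback, and at 5% sponged with a difference of up to 1 SD the test is close to nominal. Nor does the document say that the two methods differ in methylation: the sponge yields liquid saliva, collected with the same kit to the same fill line. These points stand, and they make the concern conditional.

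It can also be said that a condensed article leaves sample logs to other documents. That is fair for the recording of the method. It does not cover the stated models, which are an unadjusted Aim 1 comparison and a covariate list without the method.

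A reader might infer more than the text supports:

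- **That 20% of TBI children are sponged.** The 20% in the Study Overview is a recruitment minimum for moderate to severe TBI, graded by lowest postresuscitation GCS. It is not a count of children unable to spit when saliva is taken.
- **That OI children always spit.** The sponge rule applies to either group, and children as young as 3 may be unable to spit in both groups and at any visit. That part need not align with group-by-time.
- **That the artefact matches the planned effect.** Shifts of 0.10–0.20 SD are below the 0.26–0.45 SD equivalent.
- **That sponged children will form a latent class.** This is possible but not shown. Class size above 10% is only one of several selection criteria.
- **That the concordance check pools both methods.** The article does not say whether it does.

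**Conclusion.** The concern holds as a conditional measurement bias, not as a demonstrated error. The collection method depends on the child's condition, can change between visits, and has no term in the stated methylation models. It matters only if saliva is used for the primary methylation analyses and the two methods give different values. It could then either mimic or mask the hypothesized group-by-time pattern; the direction is unknown.

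Over the more moderate assumed values, the false-positive rate runs from essentially nominal to 0.29, as tabulated. The documents do not allow a narrower range, because they give neither the sponged share nor the method difference. The figures also assume no sponging in OI or at follow-up. BDNF protein, measured in plasma, is untouched, and so is methylation if only blood is used. The remedy is cheap and worth adopting before the biosample is chosen.

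**What to change.** 1. Record spit or sponge for every saliva sample, and recover it from collection logs for samples already taken.
2. Include it as a sample-level, time-varying term in any saliva methylation model, including Aim 1.
3. Examine the concordance of saliva with blood and CSF separately by method. CSF comes only from children with a ventricular drain, who may be among those more likely to be sponged.
4. Repeat Aims 1 and 2 in spit-only saliva as a sensitivity analysis.

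The cost is one database field, a log review and one model term. The drawback is that method is partly collinear with acute severity. The adjusted contrast will be somewhat less precise, and the spit-only analysis will lean toward less severely injured children. Sponged samples from OI children or from follow-up visits, where they exist, would help to separate method from severity.

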### Outcomes

Child neuropsychological function is assessed acutely and at each follow-up visit using the NIHTB-CB (97). The NIHTB-CB is a 30-min battery of standardized neuropsychological tests administered on an iPad. The NIHTB-CB provides norm-referenced scores for the domains of language, episodic memory, processing speed, working memory, and executive function, as well as an overall cognitive function composite score.

Parent-reported child postinjury executive, emotional/ behavioral, and adaptive functioning are measured at follow-up visits using the BRIEF-2/P, SDQ, Vineland-3, and resilience items from the CHIP. Postinjury adversity is measured using the PAT and child resilience by the CHIP.

